### Ethics Approval

The National Central Ethics Committee under the Ministry of Health and Social Development in the Republic of Kazakhstan approved this study on August 19, 2016. The study has been registered at ClinicalTrials.gov [NCT02926534].

## Results

We have completed the participant recruitment and study procedures. Currently, we are working on data processing and data analysis. The authors anticipate the preliminary results should be available by September 2017. Study results will be published in peer-reviewed scientific journals.

## Discussion

To the best of our knowledge, this is the first study in Kazakhstan that assesses COPD prevalence in the general population aged 40 to 59 years, specifically smokers, ex-smokers, and never-smokers. The study also aims to investigate COPD comorbidities and their interaction with COPD. Improving COPD preventive measures, COPD screening, identification, and registration requires obtaining this epidemiological information. Study strengths include its relatively large sample size and collection of comprehensive medical, behavioral, and other health-related data from each study participant.

However, there remain some limitations. First, the study is observational. Thus, the possibility of unidentified or unmeasured confounders exists. We are going to conduct the sensitivity analysis to assess a covariate that could eliminate the effect of smoking on COPD. Second, the study is cross-sectional, and the time when COPD occurred cannot be identified. The values of potential confounders measured in the study could differ from ones when symptoms of COPD first appeared and could be diagnosed. As a result, causal inferences cannot be made. Third, the study includes many components to be measured, which makes it impossible to employ probability sampling to select participants. The main risk of nonprobability sampling is that the distribution of important covariates in the sample will differ significantly from their distribution in the study population. We employ quota sampling to set quotas for gender and age, 2 important covariates for COPD, to balance them in the sample. In addition, we measure all known important covariates or confounders to make the desired adjustments in our data analysis. Fourth, the study is conducted in one city, Almaty, which reduces the generalizability of the study results to the country population. Finally, we expect some measurement bias that arises from errors in the data collection. For example, participants could avoid socially undesirable answers. To reduce the latter bias, all data collection procedures were tested and the research staff members were trained.

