**Conclusions:**

This is the first study in Kazakhstan that assesses prevalence of COPD and its comorbidities in the adult population aged 40 to 59 years. The results of the study will be useful for improving COPD preventive measures, better COPD screening, identification, and registration. Findings of the study will also contribute to global knowledge on the epidemiology of COPD.

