Comorbidities are frequently found in persons with COPD. Some of them have risk factors, which are the same as for COPD, particularly tobacco smoking and aging. Moreover, systemic inflammation and chronic hypoxia present in COPD patients may cause other health-related conditions. Common comorbidities include heart disease, lung cancer, osteoporosis, metabolic syndrome and diabetes, anemia, anxiety, cognitive decline, and sleep disorders [21,22]. Specific comorbidities increase mortality and poor outcome in COPD, so management of main comorbidities has been included to COPD guidelines [6].

The aim of the study is to assess the prevalence of COPD among smokers, ex-smokers, and never-smokers aged 40 to 59 years based on pulmonary function assessment (spirometry), structural changes (emphysema and large and small airway inflammation with thickening) identified by high-resolution CT, COPD symptoms, and exercise limitations. In addition, the study objectives include comparing the prevalence of health conditions considered as COPD comorbidities (heart disease, hypertension, metabolic syndrome, diabetes mellitus) in 3 study groups and their interaction with COPD.

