## Methods

### Study Design

This is an observational study with a cross-sectional design to assess the prevalence of COPD in Almaty, Kazakhstan, among individuals aged 40 to 59 years based on results of spirometry, the presence of structural changes in the lungs, and symptoms of COPD.

The study population is 3 groups of male and female residents of Almaty, the largest city in Kazakhstan, with a population of 1.7 million people, 9% of whom are aged 40 to 59 years. Members of the first group include current smokers with more than a 10 pack-year history of smoking (smokers). The second group comprises individuals who quit smoking from 1 to 5 years ago and have more than a 10 pack-year history of smoking (ex-smokers). The third group comprises persons who have never smoked regularly (ie, smoked less than 100 cigarettes in their lifetime) (never-smokers).

We recruited individuals who are 40 years of age or older because most people are at least 40 years old when the symptoms of COPD first appear [23]. The same age limit is selected for many COPD prevalence studies [24-26]. The upper age was set at 59 years to avoid survival bias [27] possibly leading to underestimating the effects of risk factors on COPD. We have taken into account that the life expectancy at birth among males was only 66 years in Kazakhstan in 2015 [28].

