### Sampling

According to the Burden of Obstructive Lung Disease (BOLD) protocol, a minimal sample size of 600 is recommended to achieve an acceptable level of precision for estimating COPD prevalence [29]. Our goal is for a sample size of 900 including 500 smokers, 200 ex-smokers, and 200 never-smokers. We have used the National Health and Nutrition Examination Surveys data to assume COPD prevalence in these 3 groups [30]. The sample size of 500 allows for achieving the precision of 3.5% with the expected prevalence of obstructive impairment of 20%. The sample size of 200 and the expected prevalence of pulmonary obstruction of 10% and 2% among ex-smokers and never-smokers, respectively, provides sample estimates with 4.2% and 1.9% precision, respectively [31].

The 3 study groups are planned to have the same gender and age distribution by implementing age-gender quota to eliminate age and gender potential confounding effect to the associations between smoking status and outcomes.

It was shown that the sample characteristics depend on recruitment method used [32]. To recruit study participants, active and passive approaches are used. Participants are recruited by using personal networks of investigators and persons who are already participating in the study (snowball), placing an advertisement of the study in social media (Facebook) targeting those individuals who are potentially eligible to participate (live in Almaty, specific age group), and meeting with the owners and managerial staff of several large companies located in Almaty to explain the benefits of participation in the study. Employees of these companies who are potentially eligible to participate in the study are contacted by phone calls.

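### The Abstract conclusion and the Discussion claim prevalence in the adult or general population aged 40 to 59, but the design supports prevalence only within three restricted smoking groups

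*Protocol article*

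**What the plan says.** Two places state a population-level claim. The Discussion says that "this is the first study in Kazakhstan that assesses COPD prevalence in the general population aged 40 to 59 years", and the sentence goes on: "specifically smokers, ex-smokers, and never-smokers". The Conclusions paragraph of the Abstract says the study "assesses prevalence of COPD and its comorbidities in the adult population aged 40 to 59 years", with no mention of smoking groups.

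The formal aim at the end of the Introduction is narrower: to "assess the prevalence of COPD among smokers, ex-smokers, and never-smokers aged 40 to 59 years".

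Study Design defines the groups. The first is current smokers above 10 pack-years. The second is "individuals who quit smoking from 1 to 5 years ago and have more than a 10 pack-year history of smoking". The third is people who smoked fewer than 100 cigarettes in their lives. Sampling sets the sizes: "Our goal is for a sample size of 900 including 500 smokers, 200 ex-smokers, and 200 never-smokers". It also gives an expected prevalence and a precision for each group separately.

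The limitations in the Discussion name non-probability sampling and the single city. They mention neither the smoking categories that belong to no group nor the fixed group mix.

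**The concern.** A prevalence for a population needs two things: everyone in it must have some chance of being sampled, and the sample's composition must either follow the population's or be weighted back to it. Here neither holds for smoking, which the Introduction lists among the main COPD risk factors. Some smoking categories have no chance of selection, and smokers make up 500/900 = 55.6% of the sample whatever their share among Almaty residents.

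The article presents its findings as a basis for COPD prevention, screening and registration, and sets the study against population figures (15.3% of adults in a neighbouring country, an estimated 1.4 million affected in Kazakhstan). A reader who takes the two claims at face value may carry a figure from this sample into that comparison. The Discussion's qualifier does not prevent this: naming smokers, ex-smokers and never-smokers without their limits reads as if the three together made up the population.

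**Working it through.** **1. What the design was sized for.** Inputs from Sampling: n = 500 at 20%, n = 200 at 10%, n = 200 at 2%. The 95% half-width is 1.96 × √(p(1 − p)/n).

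- Smokers: 1.96 × √(0.20 × 0.80/500) = 3.51 points (stated 3.5)
- Ex-smokers: 1.96 × √(0.10 × 0.90/200) = 4.16 points (stated 4.2)
- Never-smokers: 1.96 × √(0.02 × 0.98/200) = 1.94 points (stated 1.9)

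All three stated precisions reproduce. The plan is sized for three separate group prevalences, which agrees with its aim.

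**2. Who is left out.** Setting the definitions in Study Design against all residents aged 40 to 59, these people belong to no group:

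- current smokers with at least 100 cigarettes but not more than 10 pack-years;
- ex-smokers in the same range of exposure;
- ex-smokers above 10 pack-years who stopped less than 1 year ago or more than 5 years ago.

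(Inclusion and Exclusion Criteria admits exactly 10 pack-years where Study Design requires more than 10. That boundary does not matter here.)

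**3. What pooling would give.** Expected cases are 500 × 0.20 + 200 × 0.10 + 200 × 0.02 = 100 + 20 + 4 = 124, and 124/900 = 13.8%.

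**4. What a population figure might be.** The article gives no smoking distribution, so every share below is an assumption. With population shares w for the three groups and u for the omitted people, whose prevalence is q:

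prevalence = 0.20·w₁ + 0.10·w₂ + 0.02·w₃ + q·u

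q is taken from 2% (omitted people resemble never-smokers) to 20% (they resemble the smoker group).

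| Assumed shares w₁/w₂/w₃, omitted u | Sum over the three groups | Covered part only | Whole population, q = 2% to 20% |
|---|---|---|---|
| 15/5/60, 20% | 0.030 + 0.005 + 0.012 = 0.047 | 0.047/0.80 = 5.9% | 5.1% to 8.7% |
| 25/5/50, 20% | 0.050 + 0.005 + 0.010 = 0.065 | 0.065/0.80 = 8.1% | 6.9% to 10.5% |
| 35/10/40, 15% | 0.070 + 0.010 + 0.008 = 0.088 | 0.088/0.85 = 10.4% | 9.1% to 11.8% |

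That is roughly 5% to 12%. A harsher corner, with 30% omitted and the covered part split 40/10/50, reaches 0.70 × 0.10 + 0.30 × 0.20 = 13.0%.

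**5. What weighting could do.** External smoking shares could correct the mix of the covered part. They could not supply q, because nobody in the omitted categories is observed.

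**The case against.** The strongest reply is that the article already works by group. The aim is group-specific, comorbidities are to be compared across the three groups, the Electrocardiography and Physical Exam sections report by group, and each precision figure belongs to one group. Study Design states outright that the study population is the three groups and attaches the pack-year, quit-time and cigarette limits to their labels. The loose wording is confined to one sentence in the Abstract and one in the Discussion. All of this stands. It narrows the point to those two sentences and the limitations, and it shows that they go beyond the article's own aim.

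Several stronger readings are tempting and are not supported:

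- *A reader might infer that a pooled prevalence on all 900 is planned.* Nothing in the article announces one; the 13.8% is an illustration.
- *A reader might infer that Study Design misstates its population and needs rewording.* Its opening sentence is broad, but the next paragraph defines the groups.
- *A reader might infer that the error dwarfs the stated 3.5-point precision.* That precision belongs to the 500 smokers alone. At the mild end the gap is 13.8 − 11.8 = 2.0 points, and in the harsher corner 13.8 − 13.0 = 0.8.
- *A reader might infer that the sample-size benchmark is missed,* since "a minimal sample size of 600 is recommended to achieve an acceptable level of precision for estimating COPD prevalence" and no group has 600. The article does not apply that benchmark to each group, and the source that would settle its meaning is not shown.
- *A reader might infer that weighting can repair nothing.* The mix could be corrected with external shares; only the omitted categories could not.

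**Conclusion.** The point holds as one of overstated inference. The design can give prevalence within the three groups as Study Design defines them, in Almaty and subject to the non-probability sampling that the article admits. It cannot, from these data alone, give COPD or comorbidity prevalence in the adult or general population aged 40 to 59. No stated calculation is wrong.

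The omitted smoking categories and the fixed mix follow from the text and need no assumption. The size does: under the tabulated shares a pooled 13.8% would stand against roughly 5% to 12%, a ratio between 13.8/11.8 = 1.2 and 13.8/5.1 = 2.7. This uses the plan's expected rates, assumed smoking shares, and an assumed 2% to 20% prevalence in the omitted people. The direction, overstatement, depends on smokers above 10 pack-years being well below 55.6% of residents of that age, which the article does not document.

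**What to change.** - In the Abstract's Conclusions and the first paragraph of the Discussion, replace the population claim with the three groups as defined in Study Design, including the pack-year, quit-time and lifetime-cigarette limits, and name Almaty.
- State that COPD and comorbidity prevalence is reported by group, and that no pooled figure from the 900 will be presented as a population prevalence.
- Add two items to the limitations: the smoking categories that could not be selected (lighter current and former smokers; those who stopped less than 1 or more than 5 years ago), and the group mix set by design.

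Study Design, the sample size and the precision figures need no change for this point.

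The cost is a few sentences. Recruitment is complete but analysis is still under way, so the reporting rule can be fixed before results appear. The downside is that the sponsor gives up the general-population headline.

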## Abbreviations

BOLD: Burden of Obstructive Lung Disease
CAT: COPD Assessment Test
CAPI: computer-assisted personal interviewing
COPD: chronic obstructive pulmonary disease
CT: computed tomography
ECG: electrocardiogram
FEV1: forced expiratory volume in 1 second
FVC: forced vital capacity
